## Abstract

**Background:**

Urinary tract infections (UTIs) are one of the most common bacterial infections in children. In children < 7 years of age, the prevalence of one episode of symptomatic UTI has been estimated at 3–7% in girls and 1–2% in boys, whereas 8–30% of them will have one or more episodes of UTI. The use of some probiotics appears to reduce the risk of recurrence of UTIs. Since the effects of probiotics are strain-specific, the efficacy and safety of each strain has to be assessed. The main aim of this study is to determine whether probiotics (containing *Lactobacillus rhamnosus PL1* and *Lactobacillus plantarum PM1)* therapy are effective in preventing UTI in children compared to placebo.

**Method:**

A superiority, double-blind, randomised, controlled trial is being conducted. One hundred and six patients aged 3 to 18 years with recurrent UTIs in last year (defined as: ≥ 2 episodes of UTI with acute pyelonephritis/upper UTI; or 1 episode of UTI with acute pyelonephritis and ≥ 1 episodes of UTI with cystitis/lower UTI; or ≥ 3 episodes of UTI with cystitis/lower UTI) or children with ≥ 1 infection in the upper urinary tract and ≥ 1 of recurrent UTIs risk factors (congenital anomalies of the kidney and urinary tract, constipation, bladder dysfunction, myelomeningocele, sexual activity in girls) will be randomly assigned to receive a 90-day prophylaxis arm (probiotic containing *L. rhamnosus PL1* and *L. plantarum PM1*) or a 90-day placebo arm. The primary outcome measure will be the frequency of recurrence of UTI during the intervention and in the period 9 months after the intervention.

**Discussion:**

The findings of this randomised controlled trial (RCT), whether positive or negative, will contribute to the formulation of further recommendations on prevention of recurrent UTIs in children.

***Trial registration number*:**

NCT03462160, date of trial registration 12th March 2018.

## Backround

Urinary tract infections (UTIs) are one of the most common bacterial infections in children. In children < 7 years of age, the prevalence of one episode of symptomatic UTI has been estimated at 3–7% in girls and 1–2% in boys, with 8–30% of them will have one or more recurrences of a UTI [1–3].

In previously published European and global guidelines, there have been no clear recommendation for prohylaxis of UTIs. According to the current recommendations, including the Polish Society of Paediatric Nephrology, antibacterial prophylaxis should be considered in children with congenital anomalies of kidney and urinary tract (CAKUT) with a history of UTIs [1, 2, 4–7].

Some randomised studies found no beneficial effect of antibiotic prophylaxis in decreasing the frequency of UTIs or preventing renal scarring. Furthermore, the antibiotic prevention strategies was associated with bacterial resistance [3, 8].

In recent years, we have observed an increasing interest in alternative methods of UTIs prevention, such as immunotherapy and probiotic therapy [9–12]. Use of some probiotics appears to reduce the risk of UTIs. Lee and et al. conducted randomised trial in children with persistent primary vescioureteral reflux (VUR) and with history of recurrent UTIs [13] and in children with VUR < 1 year old having experienced pyelonephritis [14], comparing the effect of *L. acidophilus* to a low-dose trimethoprim and sulfamethoxazole therapy (TMP/SMX). The effect on recurrent UTIs of probiotic and antibiotic therapy did not significantly differ [13, 14]. There are also some published trials with probiotics and their influence on decreasing UTIs in adult women [15–17]. In the up-to-date research, the methodology used varied considerably [18, 19]. Since the effect of probiotics are strain specific, the efficacy and safety of each strain has to be assessed.

This study products contains a specific combination of two bacterial strains *L. rhamnosus PL1* and *L. plantarum PM1*.

It is suggested that lactobacilli bacteria had a natural ability to move along gastrointenstinal tract to the rectum and anus and from where they migrate to the urethra and vagina [20, 21]. Lactic acid-producing bacteria may positively affect the urogenital microflora due to the strong adhesion to the epithelial urogenitaly tracts and displacing uropathogenic microorganism [22, 23]. Moreover, probiotics may inhibit the growth of pathogenic microorganism by producing substances, such as lactic and acetic acid, and bacteriocins [24, 25]. They may also prevent infections by immunomodulation [23, 26]. Some intervention studies have been reported if the administration of specific *Lactobacillus* strains can prevent UTIs [27, 28].

## Methods/design

### Trial objectives and hypothesis

The investigators aim to assess the effect and safety of administration of probiotic containing: *L. rhamnosus* PL1 with *L. plantarum* PM1 in prevention of recurrent UTIs in children. We hypothesise that study product is more effective than placebo in prophylaxis of UTIs in children.

The trial is registered at ClinicalTrials.gov (NCT03462160) and any significant changes will be included there.

### Trial design

This study is designed as a randomised, placebo-controlled, double-blind, superiority trial.

### Settings and participants

The study will be performed in paediatric units of the paediatric hospital and the nephrology outpatient clinic of the Medical University of Warsaw. The recruitment started in July 2018 and should be completed within the following 3 years.

### Eligibility criteria

Participants must fulfil all inclusion criteria to be recruited for the trial:

aged from 3 to 18 years; diagnosis of recurrent UTIs in the last year, defined as: ≥ 2 episodes of UTI with acute pyelonephritis/upper UTI1 episode of UTI with acute pyelonephritis and ≥ 1 episodes of UTI with cystitis/lower UTI ≥ 3 episodes of UTI with cystitis/lower UTI [29].

or 1 infection in the upper urinary tract and ≥ 1 of UTIs risk factors: CAKUT, constipation, bladder dysfunction, myelomeningocele, sexual activity in girls; ≥ 1 episode of urinary tract infection in the last 6 months; signed informed consent.

### Exclusion criteria

Will include the following: intake of probiotic preparations for ≥ 1 month in the last 3 months; antibiotic use within last month due to any reason, known allergy to the study products, immunosuppression therapy, disease with immune deficiency, central catheter and children with other coexisting infections, e.g. meningitis, sepsis, pneumonia, otitis.

### Interventions

All participants will be provided with probiotics containing *L. rhamnosus PL1* with *L. plantarum PM1* or placebo. The placebo powder consists of a mixture of potato maltodextrin, glucose, arabic gum, pectin and silicon dioxide. The formulation is identical with the active products but without *L. rhamnosus PL1* and *L. plantarum PM1*. The appearance of the placebo will be comparable to the powder containing probiotics. Placebo as the gold standard for assessing the effectiveness of a new treatment was chosen as the comparator in our trial.

The study products (probiotic and placebo) will be manufactured and supplied by Miralex (Pila, Poland) free of charge. The manufacturer will not take part in conception and protocol preparation, design and conduct study, or in the process of analysing and interpretation of the data.

### Study procedure

Oral and written information will be given to parents of each participants and children > 16 years old. Participants will be randomised during hospitalisation or visit at outpatient clinic. Eligible patients will receive *L. rhamnosus PL1* with *L. plantarum PM1* at a dose of 10^9^ CFU (2 g) each or placebo, orally, once daily, in the evening during a meal, after dissolving the powder in lukewarm water. The probiotics or placebo will be administered for 90 days. Throughout the study period caregivers will record the UTI. Caregivers will have the right to withdraw a participating child from the study at any time and they will not be obliged to give reasons for this decision and this will not affect subsequent medical care.

In the event of UTI, the proper treatment will be implemented [6].

### Follow-up

All study participants will be followed up directly after intervention and 3, 6 and 9 months after the intervention.

### Compliance

Face-to-face interview with patients and/or caregiver and through daily patient’s diary (prepared by researchers and returned upon completion of the intervention) will be conducted to assess compliance with the study. Based on previously published trials [11, 13, 14], it seems appropriate to consider those participants receiving < 75% of the recommended doses as being non-compliant.

### Concomitant medications

The physician may consider discontinuation or modification of the UTI prophylaxis if needed.

### Outcome measures

The primary outcome measures will be the frequency of UTIs during the intervention and during the 9 months period after the intervention. The secondary outcome measures are as follows: the frequency of hospitalization due to UTI, the number of days of antibiotic therapy due to UTI.

### Participant timeline

The plan for the recruitment, intervention, evaluation and visits of participants is presented in Table 1.

**Table 1 Tab1:** Timetable of activities planned during the study

		Study period				
	Enrolment and allocation	Post allocation				Close-out (after the end of follow-up period)
Time point	Day 1	Month 3	Month 6	Month 9	Month 12	
Enrolment						
Eligibility screen	X					
Informed consent	X					
Randomisation of the participant	X					
Study product distribution	X					
Interventions						
Probiotic						
Placebo						
Assessments						
Recurrence of UTI		X	X	X	X	X
Frequencies of hospitalization due to UTI		X	X	X	X	X
No of days of antibiotic therapy due to UTI		X	X	X	X	X
Return of patient’s diary		X				
Return of non-used study products		X				
Telephone contact*			X	x	X	X

*UTI* Urinary tract infection

### Sample size

Based on data from previous studies [1–3], we assumed that the frequency of reccurences of UTIs will be 30% in the group of patients at similar age in one year. 88 patients are required to have a 90% chance of detection, as significant at the 5% level, a decrease in the primary outcome measure from 30% in the control group to 5% in the experimental group. Taking into account that 20% of the patients will be lost for follow-up, we have calculated that a total of 106 children will be needed.

A power and sample size calculator for the binary outcome superiority trial was used to estimate the study and control group.

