### Sequence generation

Randomisation list will be generated by the independent reasercher from Medical University of Warsaw. Block randomisation will be used, with a block size of 6. Randomisation codes will be revealed when all data will be collecting and final analysis will performed. Reaserchers and participants will not know the assignment to the group of patients during the study.

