### Statistical analysis

Intension-to treat (ITT) analysis will be performed, including all randomly assigned participants whom outcomes will be approachable (including dropouts and withdrawals). A per protocol analysis on the primary and secondary outcomes will be processed. This analysis will include children who have completed the entire treatment protocol as originally planned, with availability 9 months after intervention. X^2^ tests (Pearson's or Fisher's test) will be performed for binary outcome measures.

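### The target of 106 inflates 88 by a factor of 1.2 instead of dividing by 0.8, so at the planned 20% loss about 84–85 children remain, 3–4 short of the required 88 (minor)

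*Protocol article*

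**What the plan says.** The Sample size section of the protocol article gives three linked figures.

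- **Requirement:** "88 patients are required to have a 90% chance of detection, as significant at the 5% level". The effect to be detected is "a decrease in the primary outcome measure from 30% in the control group to 5% in the experimental group".
- **Loss allowance and total:** "20% of the patients will be lost for follow-up, we have calculated that a total of 106 children will be needed".

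The Method part of the abstract repeats the total: "One hundred and six patients aged 3 to 18 years". The section does not write out how 88 was inflated to 106. It says only that a calculator for a binary-outcome superiority trial was used.

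The Statistical analysis section limits the intention-to-treat set to randomised participants whose outcomes can be obtained. It limits the per-protocol set to children who completed treatment as planned and are available 9 months after the intervention.

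**The concern.** A loss allowance should leave the required number evaluable after the expected loss has occurred. Here it does not, because 20% taken off 106 leaves fewer than 88. Both analysis sets depend on outcome data being available, so children lost to follow-up are not counted back in, and the number analysed is the number left after loss.

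What is at stake is the accuracy of the sample-size statement. A reader who checks the three printed figures finds that they do not fit together. The same total serves as the recruitment target in the abstract. The effect on power has to be worked out separately, and it is small.

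**Working it through.** **Inputs**

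- Event rates 30% (control) and 5% (experimental), power 90%, significance level 5%, 88 required, 20% lost, total 106: all from the Sample size section.
- Sidedness is not stated. Two-sided is assumed.
- The allocation ratio is not stated. 1:1 is assumed, which fits two arms and "Block randomisation will be used, with a block size of 6".

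**Step 1. Reproduce 88.** Unpooled normal approximation for two proportions:

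n per arm = (z₀.₉₇₅ + z₀.₉₀)² × [p₁(1 − p₁) + p₂(1 − p₂)] / (p₁ − p₂)²

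= (1.960 + 1.282)² × (0.30 × 0.70 + 0.05 × 0.95) / 0.25²

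= 10.507 × 0.2575 / 0.0625 = 43.29, so 44 per arm and 88 in total.

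This matches the plan exactly. The other common variants do not:

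| Variant | Total |
|---|---|
| Unpooled, two-sided | 88 |
| Unpooled, one-sided | 72 |
| Pooled, two-sided | 94 |
| Pooled, two-sided, continuity-corrected | 110 |
| Pooled, one-sided | 76 |
| Pooled, one-sided, continuity-corrected | 92 |

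The 110 in this table is a different quantity from the 110 in Step 2. It comes before any allowance for loss, and the match is a coincidence.

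**Step 2. Reproduce 106.**

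- Multiplying: 88 × (1 + 0.20) = 105.6, rounded up to 106. This matches.
- Dividing: 88 / (1 − 0.20) = 110. This does not match.

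**Step 3. What 106 delivers.**

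- At 20% loss: 106 × 0.80 = 84.8, so about 84–85 evaluable, 3–4 fewer than 88.
- Largest loss that still leaves 88: (106 − 88) / 106 = 18/106 = 17.0%.
- Check of the alternative: 110 × 0.80 = 88.

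**Step 4. Cost in power by the same formula.** Power = Φ(0.25/SE − 1.960), with SE = √[0.2575 / (N/2)].

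| Evaluable N | 0.25/SE | Power |
|---|---|---|
| 88 | 3.268 | 90.5% |
| 85 | 3.212 | 89.5% |
| 84.8 | 3.208 | 89.4% |
| 84 | 3.193 | 89.1% |

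The loss is about 1 percentage point.

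**Step 5. Exact power as a cross-check.** Full enumeration of both binomials at 30% and 5%, using the uncorrected Pearson test at two-sided 5%, gives 91.8% at 44 per arm and 90.4% at 42 per arm. With 85 children it gives 90.1% or 89.9%, depending on which arm has 43. At 84–85 evaluable, exact power is therefore still about 90%.

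**The case against.** **The 20% might be meant as 20% of the 88.** On that reading 106 would be correct. The wording is against it: patients are lost from among those enrolled, and the sentence speaks of patients being lost. The document does not show the multiplier, so 1.2 is inferred from the match. The shortfall does not depend on that inference, because it follows from 88, 20% and 106 alone.

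**The effect is trivial.** This largely stands. The 88 already carries some rounding up: the formula's unrounded total is 2 × 43.29 = 86.6, so 84–85 is only about 2 children below the unrounded requirement. The 20% is a planning guess, and a loss of up to 17% is covered. No analysis or estimand changes.

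**A reader might infer that 90% power is lost.** The documents do not support this. The planning formula gives about 89%, and exact Pearson power at the same numbers is about 90%. What fails is narrower: 106 less 20% does not leave 88.

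**A reader might also infer a larger power problem because the Statistical analysis section allows either Pearson's or Fisher's test.** Fisher's test used throughout would give 85.4% at 44 per arm and 84.6% at 42 per arm. That gap does not come from the inflation step, since it is already there at the full 88 and the shortfall adds only 0.8 points. It also assumes that Fisher's test is always used. If it were used only when an expected count falls below 5 (an assumed rule), power would be 91.2% at 44 per arm. The rule for choosing between the tests may sit in an analysis plan that is not shown, so it forms no part of this point.

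**Conclusion.** The point holds as a minor arithmetic error. The stated requirement of 88, the stated loss of 20% and the stated total of 106 are inconsistent: 106 falls 4 short of 110 randomised and, at 20% loss, leaves 3–4 fewer evaluable children than 88. It covers a loss of 17.0%, not 20%.

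This part needs no assumption beyond reading the 20% as a share of those enrolled. The power figures also assume a two-sided test, 1:1 allocation and the planned rates of 30% and 5%. On those assumptions the cost is about 1 point by the planning formula, from 90.5% to 89.1–89.5%. The figures do not show an underpowered trial. The statement is wrong as written and should be corrected.

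**What to change.** Correct the loss sentence in the Sample size section in one of two ways.

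1. **Keep 106.** State that it allows for about 17% loss. Alternatively, keep the 20% and state that it leaves about 84–85 evaluable children, with about 89% power by the formula used for planning. This costs one sentence and no extra children.
2. **State 110** (88 / 0.80, or 55 per arm with 1:1 allocation). This means recruiting 4 more children. The abstract must then carry the new total.

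The first option is sufficient given the size of the effect.

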### Recruitment

The recruitment rates will be followed up monthly. Patient, recruiting clinician, the centre and the trial design will be evaluated in the event of slow and poor recruitment due to reasons at various levels.

### Sequence generation

Randomisation list will be generated by the independent reasercher from Medical University of Warsaw. Block randomisation will be used, with a block size of 6. Randomisation codes will be revealed when all data will be collecting and final analysis will performed. Reaserchers and participants will not know the assignment to the group of patients during the study.

### Allocation concealment

Allocation concealment will be processed with use of opaque, sealed, numbered envelopes. It will be implemented after getting informed consent and after entering essential, demografic information to the case report form (CRF). An independent person will assign the numbered study products in accordance with randomisation list generated by a computer.

### Blinding

The probiotic and placebo will be packaged in identical sachets. Powder will look and taste similar. The sachets will be delivered by Miralex in sealed and sequentially numbered opaque envelopes. The intervention will be blinded for all participants and investigators by the end of the study.

### Data collection and management

All participants will be ensured about data confidentiality during workshop process. All study participants will be allocated to a study identification number. Data will be collected and stored in the electronic database protected by password. Only involved researchers will have access to all participants records, CFRs, all documents, laboratory data, etc.

### Statistical analysis

Intension-to treat (ITT) analysis will be performed, including all randomly assigned participants whom outcomes will be approachable (including dropouts and withdrawals). A per protocol analysis on the primary and secondary outcomes will be processed. This analysis will include children who have completed the entire treatment protocol as originally planned, with availability 9 months after intervention. X^2^ tests (Pearson's or Fisher's test) will be performed for binary outcome measures.

### Harms

Although the occurrence of adverse events as a result of participation in the current trial is not expected, data on adverse events data will be collected. All serious adverse events will be immediately reported to the project leader who will be responsible for notifying the Ethics Committee, all participating investigators and the manufacturer of the study products.

### Auditing

Auditing for this study was not required by the Bioethics Committee.

### Ethics and dissemination

The Bioethics Committee of the Medical University of Warsaw reviewed and accepted the study protocol and template consent. If any modifications to the protocol have influence on the conducting of the study, they will be presented to the Committee. Verbal and written information about informal consent will be revealed to the caregivers. The informed consent forms will have to be singed by a parent or legal gardian prior to the randomisation. Patients may abandon from the study at any time without warring, as is documented and explained at the time of providing consent. The full protocol will be available freely due to open access publication. Abstracts will be submitted to relevant national and international conferences.

## Discussion

A precise clinical question has been posed to fill a gap in knowledge as to whether administration of *L. rhamnosus PL1* and *L. plantarum PM1* are effective in the prevention of UTIs in children. The findings of this RCT, whether positive or negative, will contribute to the formulation of further recommendations on prevention of UTIs.

## Data Availability

The datasets use and analysed during the current study will be available from the corresponding author on reasonable request. All data generated and analysed during this study will be published in the article after the completed study.

## Abbreviations

UTI: Urinary tract infection
RCT: Randomised controlled trial
CAKUT: Congenital anomalies of kidney and urinary tract
VUR: Vescioureteral reflux
TMP/SMX: Trimethoprim and sulfamethoxazole
*L. rhamnosus PL1*: *Lactobacillus rhamnosus PL1*
*L. plantarum PM1*: *Lactobacillus plantarum PM1*
CRF: Case report form
ITT: Intention-to-treat
